### Recruitment and consent

Patients will be made aware of the trial at time of surgical pre-admission. All patients attending six week post-surgical review clinic will be screened for eligibility, and if suitable, invited to participate in the trial. Written informed consent will be obtained by a suitably qualified member of the research team at study entry.

### Randomisation procedures

Randomisation will be carried out using a bespoke web-based randomisation protocol. Patients will be randomised on a 1:1 ratio to either ‘standard of care physiotherapy’ or ‘enhanced physiotherapy’. Randomisation will be stratified by centre with block allocation.

### Intervention

The specific rehabilitation protocol we will employ for TRIO is based on the current best evidence of functional rehabilitation [24]. This incorporates four categories: (1) range of motion, (2) strengthening (3) proprioception and (4) balance/gait. The specific exercises the therapist will use to achieve defined goals for each category are outlined in detail in Table 1.

**Table 1 T1:** Rehabilitation protocol

**Category**	**Description**	**Expected achievements**
Range of motion	• Prone knee flexion AROM	• AROM of 100
	• Heel props for extension PROM	• Less than 1cm effusion after exercises
	• Stationary bicycle/rowing machine for ROM stimulus and endurance	
		• Able to attain full extension
	• Hamstring, quadriceps & gastrocnemius /soleus stretching	
	• Total end range time (TERT) of 30 minutes a day until ROM guideline attained (Aim 100°)	
Strengthening	• Isometric quads	• Able to achieve voluntary quadriceps control, demonstrated by SLR without lag
	• Straight leg raise (if not able)	• Able to perform semi squat equal weight bearing between limbs
	• Partial squats to 90°	
	• Supine sub-maximal leg press or equivalent (emphasis on pain free motion and neuromuscular control vs. pure strengthening)	
	• Front and lateral step ups progressing from 10cm	
	• Resistive exercises against Theraband 90°-30° in sitting – progress to 90°-0°	
Proprioception	• Balance exercises in single leg stance	• Able to perform sit-to-stand unsupported
	• Sit to stand	• Able to perform single leg stance activities
	• Balance ball	
	• BalanceMaster / low wobbleboard if BalanceMaster not available	
	• Perturbation from soft unstable surface	
Balance/Gait	• Braiding – alternate front and back crossover steps whilst moving laterally – progress by increasing speed	• Able to complete multiple changes of direction walking without support
	• Tandem Walk forward and backwards	
	• Walk multiple change in direction on command	
	• Shuttle walking to increase stamina	

Patients in the interventional arm of the trial will see their physiotherapist once a week for structured rehabilitation; they will be expected to undertake a further two sessions of specified exercise according to the trial exercise prescription. This additional rehabilitation will be directed by the physiotherapist and reviewed at the weekly ‘contact’ session. This protocol is in marked contrast with the ‘routine standard of care’ arm, which consists of home-based exercises involving bending the knee in isolation and using the weight of the limb to strengthen the quadriceps muscle with a static knee. The participant will be asked to perform 18 sessions of unsupervised home exercise in this trial arm. For the stated ‘non-contact’ physiotherapy sessions (in both arms of the trial), the patient will be given a rehabilitation diary to document the exercise they undertake. Extra or additional physiotherapy will not be offered to the control group within the trial period. The activities of both groups will be recorded, and any patients in the control arm receiving extra physiotherapy will be documented.

### Study assessments

All the study centres involved in this project collect routine baseline data using the OKS and EQ-5D. These data will be accessed retrospectively for recruited patients at the individual centres.

At the study baseline (six weeks post-operation) an OKS will be completed and eligible patients consented and randomised. Once consent has been obtained, the additional trial Health Economics Questionnaire and EQ-5D questionnaire will be completed. Physiotherapy pre-intervention assessment will occur two weeks following this (and TUG test performed). Following either study intervention, all patients will have a second (post-intervention) physiotherapy review (OKS, TUG, EQ-5D and Health Economics Questionnaire). At six months and one year post-operation, the OKS, EQ-5D, Health Economics and Satisfaction questions will be assessed by postal questionnaire (Table 2).

**Table 2 T2:** Study assessments by time point

**Time point**	**Pre-operation**	**6 weeks**	**8 weeks**	**14 weeks**	**6 months**	**1 year**
OKS	X	X		X	X	X
EQ-5D	X	X		X	X	X
Patient demographics		X				
Pain score VAS		X		X	X	X
Health economics questionnaire		X		X	X	X
TUG			X	X		
Satisfaction questionnaire					X	X

Trial baseline is at six weeks post-operation. Pre-operative data will be accessed retrospectively. Assessment timeframes are calculated from the date of surgery.

### Safety assessment

As the study is a non-Clinical Trial of an Investigational Medicinal Product (CTIMP) with an intervention of additional physiotherapy, there is not deemed to be a significant risk to patient safety. In the case of adverse events, participants will be advised to seek medical advice through their general practitioner. Specific adverse events such as treatment withdrawals and missed treatments due to pain will be collected through the study case report form. Patient reported outcomes will measure knee pain using a Visual Analogue Scale (VAS) and global health state via the EQ-5D.

### Sample size calculation

The sample size for TRIO is 400 patients (200 per arm). This was determined from previous research. The power calculation (Table 3) is based on the accepted change in the OKS that is considered clinically significant and of interest when comparing interventions (3 points) [16]. Typical one year change scores for the OKS are 16 points with a reported standard deviation of 9.2 [3,4].

**Table 3 T3:** Power calculation

**Difference**	**Size**	**Power**
3	150	80%
3	200	90%

Two-sample *t*-test, alpha = 0.05 (two-sided), assumed SD = 9.2.

A large prospective cohort is required to achieve the desired numbers of poorly functioning knees; therefore the study will recruit from multiple major centres. Based on reported poor outcome rates of approximately 20%, and allowing for a potential of up to 20% of eligible patients being unwilling to be randomised, we aim to screen 2,750 patients prospectively at the six-week post-surgical review to identify 550 eligible, poorly functioning patients and to achieve recruitment (randomisation) of 440. Allowing for a further 10% loss to follow-up in the RCT will yield the 400 patients we require.

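### The 90% power is right for its inputs but not justified for the planned ANCOVA, and both calculation and analysis treat patients of the same physiotherapist as independent

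*Protocol article*

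**What the plan says.** The Sample size calculation section of the protocol article takes a 3-point difference in OKS as the target. It gives the source of its variability as follows: "Typical one year change scores for the OKS are 16 points with a reported standard deviation of 9.2". The Table 3 footnote confirms that this value enters a two-sample t-test directly: "alpha = 0.05 (two-sided), assumed SD = 9.2". Table 3 lists 80% power for 150 per arm and 90% for 200 per arm. Recruitment is set at 440: "Allowing for a further 10% loss to follow-up in the RCT will yield the 400 patients we require".

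The Statistical analysis section plans something different from a t-test on change. It compares mean OKS at one year by ANCOVA, adjusting for the OKS at randomisation, which is the six-week score. That score is the only adjustment named. Under Inclusion criteria, only patients with a six-week OKS of 26 or less can enter.

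On delivery of treatment, the Intervention section says: "Patients in the interventional arm of the trial will see their physiotherapist once a week for structured rehabilitation". Study design puts this at six supervised contact sessions out of 18. Controls have an initial and a final physiotherapist review, with unsupervised home exercise in between.

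**The concern.** There are two separate points.

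**The SD.** The power of an ANCOVA depends on the residual SD of the outcome given the covariate. The value used is the SD of a change score in typical knee replacement patients. The section does not name the starting point of that change. A typical 16-point one-year change suggests the pre-operative score, but that is an inference. On either reading it is not the residual SD of one-year OKS given six-week OKS in slow recoverers, and the article gives no argument for carrying it over.

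**Independence.** Patients treated over several sessions by the same physiotherapist may have correlated outcomes. A t-test calculation and an ANCOVA with only a baseline covariate both assume that they do not. What is at stake is not only power. If the correlation is above zero, the reported standard error is too small, the 95% confidence interval too narrow and the type I error above 5%.

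**Working it through.** **Inputs from the protocol:** difference 3; SD 9.2; two-sided alpha 0.05; 200 per arm required; 440 randomised with 10% loss, so 440 × 0.9 = 396, or 198 per arm.

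**Inputs not in the protocol, assumed here:** one-year SD 9 to 11; correlation r of six-week with one-year OKS 0.3 to 0.6; therapist ICC 0.01 to 0.05; 10 to 20 patients per therapist (m).

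**1. The plan's own figure.** A t-test with SD 9.2 gives 80.4% at 150 per arm and 90.2% at 200 per arm, so Table 3 reproduces. The t-test needs 199 per arm for 90% power. The planned 200 therefore contains no allowance for clustering.

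**2. Sensitivity to the SD.** Power ≈ Φ(3 / (s·√(2/198)) − 1.96), where s is the residual SD:

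| Residual SD | Power, 198 per arm |
|---|---|
| 8.0 | 96.2% |
| 9.2 | 90.1% |
| 10.0 | 84.7% |
| 11.0 | 77.4% |

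With s = SD at one year × √(1 − r²), the assumed ranges run from 9 × √(1 − 0.36) = 7.2 to 11 × √(1 − 0.09) = 10.5. The power runs from 98.6% down to 81%. The range contains 90%, so the mismatch could favour the trial or count against it.

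**3. Sensitivity to clustering in the intensive arm only, SD 9.2.**

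- SE assuming independence = 9.2 × √(2/198) = 0.925.
- True SE = 9.2 × √(D/198 + 1/198), with D = 1 + (m − 1) × ICC.
- Type I error of the unadjusted test = 2Φ(−1.96 × 0.925 / true SE).
- Power of the adjusted test = Φ(3 / true SE − 1.96).
- Power of the unadjusted test = Φ((3 − 1.96 × 0.925) / true SE).

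| ICC, m | D | True SE | SE increase | Type I error, unadjusted | Power, adjusted | Power, unadjusted |
|---|---|---|---|---|---|---|
| 0.01, 10 | 1.09 | 0.945 | 2% | 5.5% | 88.8% | 89.6% |
| 0.02, 10 | 1.18 | 0.965 | 4% | 6.0% | 87.4% | 89.1% |
| 0.03, 15 | 1.42 | 1.017 | 10% | 7.5% | 83.9% | 87.9% |
| 0.05, 20 | 1.95 | 1.123 | 21% | 10.7% | 76.2% | 85.5% |

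The last row is extreme: 20 patients per therapist means only about 198/20 ≈ 10 therapists in the intensive arm. The two tests must be kept apart. The unadjusted test keeps more power because it is anti-conservative; the adjusted test holds its level at the price of the lower power.

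**4. Can the covariate make up the loss?** Reading 9.2 as the one-year SD, r = 0.3 gives a residual SD of 8.78. With ICC 0.02 and m = 10, adjusted power is then 90.3%. The lost power is recovered, but the ratio of true to reported standard error is still 1.04.

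**The case against.** The strongest reply is that nothing here shows the power to be below 90%. That stands. The figure is right for its inputs, and the plausible range for the SD lies on both sides of it. A reader might infer that the trial is underpowered, or that its power is known to differ from 90%; the protocol gives too little to support either reading.

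A reader might also argue that selecting slow recoverers must change the SD. That does not follow. Selection is on the six-week OKS, which is the ANCOVA covariate. Under a linear model with constant variance, such selection leaves the residual SD unchanged, although it can weaken the correlation.

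On clustering, the protocol gives no ICC, no number of therapists and no caseload, and does not say whether the same therapists treat both arms. If they do, the effects are smaller than in the table. A standardised exercise protocol and a postal outcome at one year, long after the 14-week review, may both keep the ICC low. Definite inflation of the type I error is therefore not shown.

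Finally, a therapist term could sit in an analysis plan that is not shown. That tempers the modelling request. It does not affect the power statement, which the article sets out in full and without qualification.

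**Conclusion.** The point holds in a limited form. The 90% in Table 3 is correct arithmetic on an SD that the protocol does not connect to its primary analysis. It is unsupported for that analysis rather than shown to be wrong, and the direction of any error is unknown.

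The independence assumption is the more consequential part, because its effect on the confidence interval runs one way: for any ICC above zero the interval from the stated ANCOVA is too narrow. The size rests entirely on assumed values and is modest in the milder cases (2% to 4% on the standard error, 5.5% to 6.0% type I error) and large only in the extreme one. A gain from the covariate may offset the lost power but cannot correct the interval. This is a worthwhile, cheap improvement and not a fatal flaw.

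**What to change.** 1. Record the treating physiotherapist for every patient. Recruitment was still open when the article was submitted, and this is easiest to collect during the trial.
2. Make the primary analysis a partially nested mixed model: one-year OKS adjusted for six-week OKS, with a therapist random effect in the intensive arm.
3. Restate Table 3 as power for the ANCOVA over a stated range, for example residual SD 8 to 11 and therapist ICC 0 to 0.05, giving the assumed caseload and correlation and the reason for any SD carried over from change scores.

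No increase in recruitment is proposed. The cost is one data field, a slightly wider confidence interval if the ICC is above zero, and a power figure that may look less favourable than 90%.

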## Background

Knee osteoarthritis is an extremely common and extremely disabling condition, often ultimately requiring surgical intervention. Total knee replacement (TKR) is an increasingly common procedure with over 75,000 knee replacements performed each year in the UK alone [1]. Projections of future surgical volume suggest further great increases year on year [2]. TKR is highly effective at reducing pain and improving physical function in patients with end stage osteoarthritis. Around 20% of patients however report dissatisfaction with their post-operative outcome, twice the rate following total hip replacement [3-6].

Physiotherapy is a commonly employed intervention to address dysfunction following TKR; though the efficacy of this is unknown. A previous study suggested that post-operative physiotherapy was not effective at improving the patients’ one year outcome, when applied uniformly to all patients after knee replacement [7]. Clinically, patients performing poorly post-operatively are often referred for physiotherapy review; however no study has specifically assessed patients that perform poorly post-operatively. Demonstration of the effectiveness of post-operative physiotherapy management in this ‘at risk’ group would provide support for specific policy to address this substantial population.

A recent Cochrane review examined multidisciplinary rehabilitation programmes following hip and knee joint replacement and concluded that home-based care may be beneficial; but stressed the low quality of the current evidence-base and surmised that further high quality research is needed [8]. Unspecified post-operative physiotherapy applied to a whole cohort of patients who had undergone knee replacement did not find a significant improvement over the control group one year following surgery [7]. However as the majority of patients had a good result, it was not possible to determine if targeted intensive physiotherapy would have helped the patients destined to have a poor outcome.

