### Exclusion criteria

1. Patients undergoing revision knee arthroplasty or fully constrained knee arthroplasty.

2. TKR for a diagnosis other than osteoarthritis.

3. Patients unable to attend the study physiotherapy intervention centres.

4. Procedures done purely for pain relief (such as for patients with no walking capacity).

5. Patient’s already receiving on-going structured post-operative exercise rehabilitation.

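### Minor: 440 randomised less 10% leaves 396 patients, not 400, and the 2,750 screening target allows nothing for exclusions and uses a 20% rate not tied to the entry criterion

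*Protocol article*

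**What the plan says.** The section Sample size calculation sets the requirement: "The sample size for TRIO is 400 patients (200 per arm"). Table 3 supports it with a two-sample t-test for a difference of 3 OKS points, "alpha = 0.05 (two-sided), assumed SD = 9.2", giving 80% power at 150 and 90% at 200.

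The section then works down from screening to analysis. The yield is introduced as "Based on reported poor outcome rates of approximately 20"%. Applied to 2,750 patients screened at the six-week review, it gives 550, described as both eligible and poorly functioning. Up to 20% of eligible patients are expected to decline, leaving 440 randomised. The last step is: "Allowing for a further 10% loss to follow-up in the RCT will yield the 400 patients we require".

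Three other sections bear on this:

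- Inclusion criteria define a poor outcome as OKS of 26 or less at the first post-operative review, six weeks after surgery.
- Exclusion criteria remove, among others, patients who cannot get to the physiotherapy centres and those "already receiving on-going structured post-operative exercise rehabilitation".
- Recruitment and consent says that everyone attending the six-week clinic is screened.

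Study population gives the target as 440 recruited over a planned 18 months.

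**The concern.** Two things do not fit.

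First, the last step is wrong as arithmetic. Taking 10% off 440 does not return 400. Adding 10% to the required number is not the inverse of losing 10% of the randomised number.

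Second, the step from 2,750 to 550 merges two different proportions: the share of patients who perform poorly, and the share of those who also satisfy every other criterion. A single 20% is used for the first, and the second is implicitly 100%. The refusal allowance cannot absorb the exclusions, because it is applied to patients already counted as eligible. The 20% also comes without an instrument, cut-off or time point, whereas entry depends on a specific score threshold at a specific visit.

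At stake are the accuracy of a stated sample size figure and the realism of the screening volume and 18-month recruitment period.

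**Working it through.** **Inputs** (Sample size calculation, unless noted): required 400 analysed, 200 per arm; difference 3; SD 9.2; two-sided alpha 0.05; yield 20%; refusal 20%; loss to follow-up 10%; 2,750 screened. Allocation is 1:1 (Randomisation procedures). I assume equal loss in both arms.

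**1. The plan's power figures are reproduced.** The standardised difference is 3 / 9.2 = 0.326. Two-sample t-test power:

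| Analysed per arm | Power |
|---|---|
| 150 | 80.4% |
| 198 | 89.9% |
| 199 | 90.1% |
| 200 | 90.2% |

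Table 3 is correct: 150 and 200 per arm give 80% and 90%. The smallest number reaching 90% by the t-test is 199 per arm.

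**2. The plan's chain, step by step.**

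- Eligible: 2,750 × 0.20 = 550, as stated.
- Randomised: 550 × 0.80 = 440, as stated.
- Analysed: 440 × 0.90 = 396. The plan states 400.

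The 440 equals 400 × 1.10. The correct inflation is 400 / (1 − 0.10) = 444.4, so 445. Equivalently, 440 randomised leaves 400 only if loss is 40 / 440 = 9.1%.

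**3. Size of the slip.** The shortfall is 4 patients, or 1%. Power at 198 per arm is 89.9% by the t-test (90.1% by the normal approximation), against 90.2% at 200. To deliver 400 under the plan's own rates would take 445 randomised and 445 / (0.80 × 0.20) = 2,781.25, so 2,782 screened.

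**4. Allowance for exclusions.** Since 2,750 × 0.20 is exactly 550, the implied share of poor performers failing any other criterion is zero. The protocol gives no figure for this share, so the following are assumptions. Screening needed to keep 440 randomised is 440 / [0.80 × 0.20 × (1 − x)]. Months are 18 × screened / 2,750, assuming a constant screening rate.

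| Assumed share excluded, x | Screened | Months |
|---|---|---|
| 0 (plan) | 2,750 | 18.0 |
| 5% | 2,895 | 18.9 |
| 10% | 3,056 | 20.0 |
| 20% | 3,438 | 22.5 |

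**5. The 20% rate.** The protocol gives no rate for OKS of 26 or less at six weeks. With no exclusions, an assumed true rate of 15% would need 440 / (0.80 × 0.15) = 3,667 screened, and 25% would need 440 / (0.80 × 0.25) = 2,200. The error could go either way.

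**The case against.** The best defence is that none of this matters much. Four patients out of 400 is rounding, the inputs are themselves qualified as approximate or upper limits, and Table 3 reports whole percentages. The planned analysis is also an ANCOVA on six-week OKS, not the unadjusted t-test used for sizing. If 9.2 is read as the SD of the one-year score, an assumed baseline correlation of only 0.1 makes 198 per arm worth 198 / (1 − 0.01) = 200. All of that stands as to size. It does not make the sentence true.

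On screening, 2,750 is an aim and the recruitment target is 440, so a poor yield is met by screening more. That stands too, and it limits the consequence to workload and time. Exclusions such as revision surgery or another diagnosis could have been removed before the 2,750 are counted. That is less plausible for inability to attend or current rehabilitation, which bear on the patient's situation at the review.

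A reader might go further in three ways that the protocol does not support:

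- **That the 20% is the dissatisfaction rate.** The Background says "Around 20% of patients however report dissatisfaction with their post-operative outcome", and the figures match. But the sample size section speaks of poor outcome rates and cites no source there. The link is an inference.
- **That power falls well below 90%.** If 10% to 20% of poor performers were excluded and recruitment stopped after 2,750 screened, power would be 86.6% to 82.5%. The protocol gives no exclusion rate and does not say that recruitment stops at 2,750. Nor does the Background's remark that poor performers are often referred for physiotherapy review show that many are already in structured rehabilitation by six weeks.
- **That the results would apply to the wrong population.** Entry is defined by the OKS threshold at six weeks, whatever prevalence was guessed for planning, so the population to which results apply is not in doubt.

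**Conclusion.** The point holds as a minor one. The statement that 440 randomised yields 400 is wrong as written: the figure is 396, with 89.9% power by the t-test, which is about 90% when rounded. The screening target treats every poor performer as eligible and uses a 20% rate not tied to OKS of 26 or less at six weeks.

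The first part rests only on the protocol's own numbers and equal loss between arms. The second is also read directly from the protocol, but its size cannot be known from it: the screening volumes for non-zero exclusion, and for rates other than 20%, are illustrations under assumed values. Provided recruitment continues to 440 randomised, the effect is on screening volume and recruitment time. Power is affected only if recruitment is cut short. Neither the validity of the comparison nor the planned analysis is touched.

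**What to change.** - Replace the final sentence of the sample size section with a statement that 440 randomised and 10% loss gives about 396 analysed, 198 per arm, with 89.9% power under the Table 3 assumptions. If exactly 400 analysed is to be kept as a requirement, the randomised number should read 445.
- Restate the screening target as 440 / (a × b × 0.80), where a is the share of screened patients with OKS of 26 or less at six weeks and b is the share of those who meet all other criteria. Recruitment was already under way when the article was submitted and all clinic attenders are screened, so both shares can be tallied from the screening log.
- Check the resulting number against the planned 18 months.

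The cost is a corrected sentence and a tally of existing records. Keeping 440 requires no additional patients, and the design and analysis do not change.
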